#### 2.13.5. Health Outcomes

Relevant pregnancy and infant outcomes include gestational age at delivery, mode of delivery, preterm birth, pregnancy-induced hypertension, polyhydramnios, edema, large-and-small-for-gestational age, neonatal hypoglycemia, and admission to a special care nursery.

Gestational weight gain recorded in medical records (and cross-referenced against self-reported weight at the 36-week survey) will be calculated by subtracting pre-pregnancy weight from the last recorded pregnancy weight. Gestational weight gain will also be classified as above, below, or within recommendations according to the Institute of Medicine cut-offs [38] based on pre-pregnancy body mass index.

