The primary aim of this study is to determine the effectiveness of a dietary intervention called ‘*The Healthy Gut Diet*’ on reducing the diagnosis of GDM in pregnant women with one or more specified risk factors. We hypothesize that there will be fewer women diagnosed with GDM in the intervention group and this effect will be enhanced amongst women who adhere closest to the dietary recommendations. The secondary aim is to understand whether dietary intervention can modulate the gut microbiota compared with the usual care group and if this effect is enhanced in women who closely adhere to the dietary intervention compared to those who are less adherent. The third aim is to compare the maternal and infant outcomes of women enrolled in the dietary intervention and those in the usual care group.

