### 2.2. Setting

The study is open to all pregnant women who meet the criteria who are birthing at public or private maternity facilities in Queensland, Australia. Geographically, Queensland is the second-largest state/territory and third-most populous state in Australia. Between 60,000 and 62,000 babies are born in Queensland annually. Nationally, the incidence of GDM is 16% [2].

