### 2.10. Usual Care (Control Group)

Participants in both groups undertake all usual antenatal appointments according to their selected model of antenatal care. The control group also receives a 3 min video providing brief advice on general healthy eating in pregnancy according to the Australian Dietary Guideline [29] recommendations and a link to the electronic version of the Guidelines. Women in the control group complete all data collection tasks but do not see the study dietitian or receive additional support such as text messages or access to private social media pages.

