Dietary behavior goals set by women in the intervention group will be recorded at the initial counseling appointment by the dietitian. Women will be contacted at two time points in trimester 2 and 3 to complete a 24 h recall with a trained dietitian, using the multi-pass method. Maternal and infant outcome data, including GDM diagnosis and gestational weight gain, will be collected from medical records. At baseline and 36 weeks, women will provide stool samples using a self-collection sample kit provided by Microba Life Sciences [27]. Microba is a precision microbiota science company that will be providing high quality taxonomic, functional data and sample quality metrics from the microbiota sampling kits. Microba use shotgun metagenomic sequencing using the NovaSeqTM 6000 (Illumina, San Diego, CA, USA) with 2 × 150 bp paired-end chemistry at a target depth of 3 Gb per sample. Species classification will be determined with the Microba Community Profiler (v2), which uses a curated set of genome sequences from the public domain and Microba proprietary data (Microba Genome database, MGDB) a validated pipeline for producing comprehensive and accurate species profiles of human gastrointestinal samples [27]. All data (excluding microbiota data) will be collected and stored using the online data capture tool called REDCap 13.10.6.

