### 2.14. Sample Size

The initial sample size calculation was based on the original eligibility criteria (previous GDM diagnosis), which assumed a background incidence of 50% (35 to 80% of women with a prior GDM diagnosis will develop it in subsequent pregnancies [46]). The original recruitment target of 40 women per group provided 80% power to detect a difference of 50% diagnosis rate in the control group and 25% in the intervention group (with a two-sided 5% significance level). However, as the changes to protocol outlined in Section 2.8 to include women with one or more risk factors for GDM have variably altered the background incidence of GDM, it is difficult to estimate the sample size needed for this trial. Therefore, a target of 120 women has been set on the basis that this is a pilot RCT, considering how many participants we can feasibly recruit within the study’s budget and timeline.

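### Neonatal hypoglycemia is compared between arms from routine records with no common glucose test stated; if maternal GDM prompts testing, an arm with fewer GDM diagnoses would record fewer events without any true difference

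*Protocol article*

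**What the plan says.** All references are to the protocol article.

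- Section 2.13.5 (Health Outcomes) names the infant outcomes, among them "large-and-small-for-gestational age, neonatal hypoglycemia, and admission to a special care nursery".
- Section 2.11 (Data Collection) fixes the source: "Maternal and infant outcome data, including GDM diagnosis and gestational weight gain, will be collected from medical records".
- The Introduction fixes the comparison: "The third aim is to compare the maternal and infant outcomes of women enrolled in the dietary intervention and those in the usual care group".
- Section 2.2 (Setting) admits women "birthing at public or private maternity facilities in Queensland, Australia", and section 2.10 leaves antenatal care to each woman's chosen model: "Participants in both groups undertake all usual antenatal appointments according to their selected model of antenatal care". Neonatal care, including any glucose test, is therefore whatever the place of birth does.
- The Introduction also gives the expected direction for the primary outcome: "We hypothesize that there will be fewer women diagnosed with GDM in the intervention group".

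Neither the text nor Table 2 describes a glucose test applied to every infant. The article does not say whether a GDM diagnosis changes which infants are tested.

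**The concern.** Hypoglycemia reaches a medical record only if the infant's glucose was measured. If maternal GDM makes measurement more likely, ascertainment depends on a post-randomization variable that is also the trial's primary outcome. Randomization does not protect against this. Nor does the blinding of analysts in section 2.6, because detection takes place at the bedside.

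The distortion would favor the hypothesis. An arm with fewer GDM diagnoses would have fewer infants tested and fewer events recorded, even if the infants were equally healthy. Part of a lower recorded rate might be real, but without knowing who was tested the two parts cannot be told apart. The Discussion says the pilot is meant to inform later studies and their sample sizes, so a distorted estimate matters even where no test is significant.

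**Working it through.** The article gives no figure for neonatal hypoglycemia or for neonatal testing, so there is no stated figure to reproduce. The check asks how large the distortion would be under stated assumptions.

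**Inputs**
- GDM rates, control v diet: 50% v 25% from section 2.14, which ties them to the earlier, prior-GDM eligibility ("provided 80% power to detect a difference of 50% diagnosis rate in the control group and 25% in the intervention group"); 30% v 20% (assumed); and 16%, the national incidence in section 2.2, v 8% (assumed).
- About 60 women per arm: 120 in total, allocated 1:1.
- Assumed: every infant of a GDM mother is tested, a share *t* of the others is tested, untested infants count as event-free, and the true risk *h* is the same for all infants in both arms.

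**Formula**

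Tested share in an arm with GDM rate *g*: g + (1 − g)·t. Recorded rate: h·[g + (1 − g)·t]. In the ratio of the two arms *h* cancels, so the relative risk under no effect is the ratio of tested shares, diet over control.

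| GDM, control v diet | t | Tested, control | Tested, diet | Relative risk under no effect |
|---|---|---|---|---|
| 50% v 25% | 0.1 | 55.0% | 32.5% | 0.59 |
| 50% v 25% | 0.2 | 60.0% | 40.0% | 0.67 |
| 50% v 25% | 0.6 | 80.0% | 70.0% | 0.88 |
| 30% v 20% | 0.1 | 37.0% | 28.0% | 0.76 |
| 30% v 20% | 0.2 | 44.0% | 36.0% | 0.82 |
| 30% v 20% | 0.6 | 72.0% | 68.0% | 0.94 |
| 16% v 8% | 0.1 | 24.4% | 17.2% | 0.70 |
| 16% v 8% | 0.6 | 66.4% | 63.2% | 0.95 |

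If testing does not depend on maternal GDM, or the arms have equal GDM rates, the ratio is 1.00.

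**In events.** Take h = 10%, t = 0.2 and 60 per arm.
- 30% v 20%: recorded rates 4.4% v 3.6%, or 2.6 v 2.2 expected events. The chance of a significant result (two-sided 5%, Fisher's exact test) in the diet's favor is about 0.7%.
- 50% v 25%: 6.0% v 4.0%, or 3.6 v 2.4 events. The chance is about 2.0%.

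With h = 15–30%, 95–100% testing in GDM infants and 10–50% in the others, a normal approximation puts this chance at about 3–18% across the three pairs of GDM rates, against a nominal 2.5% in that direction. The upper end needs 50% v 25%; at 30% v 20% it is about 3–7%.

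**Restricting to tested infants.** This does not remove the problem. Take 50% v 25%, t = 0.2, and a risk of 15% in GDM infants, with risks within each GDM group the same in both arms. Tested infants are then 50 GDM and 10 non-GDM per 100 births in control, and 25 and 15 in the diet arm.
- Risk 10% in tested non-GDM infants: control (7.5 + 1.0)/60 = 14.2%; diet (3.75 + 1.5)/40 = 13.1%; ratio 0.93.
- Risk 30%: control (7.5 + 3.0)/60 = 17.5%; diet (3.75 + 4.5)/40 = 20.6%; ratio 1.18.

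The tested-infant ratio moves to either side of 1 through the mix of infants alone.

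**The case against.** **The premise comes from outside the documents.** The article nowhere says that a GDM diagnosis prompts neonatal testing, and without that link the distortion is zero. This stands, and the point must be worded as conditional. The testing status of each infant would settle it, and that is what the fix collects.

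**An article condenses a fuller protocol.** Thresholds, denominators and rules for untested infants may be set there, and their absence here is no fault. The point rests on what the article does fix: the record source and the between-arm comparison. Later analysis rules cannot recover glucose values that were never measured.

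**The largest figures use superseded rates.** True: section 2.14 ties 50% v 25% to the earlier eligibility. The 0.67 at those rates should not be the headline; the same testing assumption gives 0.82 at 30% v 20%.

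**Testing of other infants may be targeted at risk.** If higher-risk infants without maternal GDM are tested preferentially, fewer events are missed. With equal overall risk in the two GDM groups, *t* can be read as the share of true events detected among non-GDM infants. At 80% detected, the ratio is 0.84/0.86 = 0.98 for 30% v 20% and 0.85/0.90 = 0.94 for 50% v 25%. The distortion shrinks but keeps its direction.

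**The effect is about one event or less at h = 10%.** This also stands. A reader might infer that the trial is likely to report a falsely significant neonatal benefit, or that any fall in recorded hypoglycemia would be an artifact. The documents support neither: the sample is small, sampling error is larger than the distortion, and part of a fall could be real.

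**Conclusion.** The concern holds in conditional form. The plan compares neonatal hypoglycemia between arms from routine records with no common test stated. If infants of mothers with GDM are tested more often, an arm with fewer GDM diagnoses will show fewer recorded events with no true difference. With full testing in GDM infants, 10–60% in the others and equal true risk, the relative risk under no effect is about 0.76–0.94 at 30% v 20% (assumed) and 0.59–0.88 at the superseded 50% v 25%.

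This affects one secondary outcome in a pilot; the primary outcome is untouched. The harm is mainly a distorted estimate that leans toward the hypothesis. It is worth correcting because the remedy is cheap and testing status must be abstracted to be available at analysis.

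**What to change.** In section 2.13.5:

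1. Abstract from the same infant record whether neonatal glucose was measured.
2. Report by arm the proportion of infants tested and hypoglycemia among all infants. Give hypoglycemia among tested infants, and the figures by maternal GDM status, as descriptive only, since both condition on events after randomization.
3. State that the all-infant comparison is open to detection differences that follow from the GDM diagnosis, so that a lower recorded rate alone is not presented as a neonatal benefit where testing differs between arms.

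Do not make agreement with the tested-infant results a condition for concluding benefit. On the figures above, that ratio can run from 0.93 to 1.18 when risks within each GDM group are equal between arms, so agreement neither confirms nor refutes benefit.

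The cost is one extra abstraction field, one table and a more cautious conclusion. No change to clinical care is involved.

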### 2.14. Sample Size

The initial sample size calculation was based on the original eligibility criteria (previous GDM diagnosis), which assumed a background incidence of 50% (35 to 80% of women with a prior GDM diagnosis will develop it in subsequent pregnancies [46]). The original recruitment target of 40 women per group provided 80% power to detect a difference of 50% diagnosis rate in the control group and 25% in the intervention group (with a two-sided 5% significance level). However, as the changes to protocol outlined in Section 2.8 to include women with one or more risk factors for GDM have variably altered the background incidence of GDM, it is difficult to estimate the sample size needed for this trial. Therefore, a target of 120 women has been set on the basis that this is a pilot RCT, considering how many participants we can feasibly recruit within the study’s budget and timeline.

## 3. Results

Recruitment commenced in January 2023 and will continue until 120 women have been recruited or until April 2024 (whichever comes first). Data will be analyzed following completion of all data collection for the final participant, which is anticipated to occur by October 2024. At the time of manuscript submission, 503 women had registered their interest in the study and 74 women had consented and were randomized into either control (*n* = 36) or intervention (*n* = 38) groups.

## 4. Discussion

There is good evidence to suggest that the gut microbiota play a role in the development of GDM. To the best of our knowledge, there have been no dietary interventions aimed at improving ‘gut health’ in pregnancy for the purpose of preventing GDM. One prospective observational study involving 41 women with GDM showed that participants who were adherent to standard GDM nutritional recommendations had better metabolic and inflammatory outcomes and exhibited a significant decrease in the Bacteroides species [22]. To date, there have been no prospective trials used to evaluate the impact of dietary modulation of the gut microbiota and its role in the development of GDM. This pilot RCT will evaluate the effectiveness of the *Healthy Gut Diet* in preventing GDM in women with one or more risk factors and will examine the relationship between dietary intake and the gut microbiota during pregnancy.

Although this is the first RCT to target the gut microbiota in pregnant women with the aim of preventing GDM, there was a recent dietary intervention trial targeting the gut microbiota in pregnant women with the aim of improving maternal diet [25]. In this study, women in the intervention group significantly improved the quality and variety of their diet and their intake of pre- and pro-biotic foods from baseline to follow-up compared to the control group [25]. The impact of such dietary changes on maternal and infant gut microbiota composition for this study has yet to be determined.

Studies investigating changes in the gut microbiota during pregnancy are limited and have yielded mixed results regarding the remodeling of the microbiota during pregnancy. Some studies report dramatic shifts to the gut microbiota across pregnancy trimesters [47,48], whilst others suggest a relatively stable microbial profile [49,50,51]. Yang et al. linked variations in composition and function with GWG, age, residency status, pre-pregnancy BMI, and gestational diseases [51], suggesting that individual heterogeneity is the major force that shapes the microbiota in pregnancy, as opposed to gestation-age variations. By adequately controlling for confounding factors, we anticipate that gestational age variations will have little impact on the result.

The findings of this study will advance the current knowledge in this field in terms of using a dietary approach to modulate the pregnant gut microbiota with the aim of preventing GDM, as well as behavior change theory. Potential outcomes (other than the development of GDM) may include fewer pregnancy complications, pregnancy weight gain within recommendations, and improved dietary intake. The postpartum follow-up for this study is designed to look at barriers and enablers of adherence to a Healthy Gut Diet, as well as longer-term sustainment of dietary interventions enhanced using BCTs.

## Figures and Tables

**Figure 1 nutrients-15-04653-f001:**
[figure not shown]
Flow chart for the control and intervention groups for the study on the Healthy Gut Diet with regards to preventing gestational diabetes.

**Table 1 nutrients-15-04653-t001:** Behavior change techniques (BCTs) [33] used in the Healthy Gut Diet Study.

BCT Category	BCT	Dietitian Education	SMS
Goals and planning	Goal setting (behavior) (1.1)	✔	✔
	Problem solving (1.2)	✔	✔
	Goal setting (outcome) (1.3)	✔	
	Action planning (1.4)	✔	✔
	Review behavior goal(s) (1.5)	✔	✔
	Discrepancy between current behavior and goal (1.6)	✔	
	Behavioral contract (1.8)	✔	
	Commitment (1.9)	✔	
Feedback and monitoring	Monitoring of behavior by others without feedback (2.1)	✔	
	Feedback on behavior (2.2)	✔	
	Self-monitoring of behavior (2.3)		✔
Social Support	Social support (unspecified) (3.1)	✔	✔
	Social support (practical) (3.2)	✔	
	Social support emotional (3.3)		✔
Shaping knowledge	Instruction on how to perform the behavior (4.1)	✔	✔
Natural consequences	Information about health consequences (5.1)	✔	✔
Association	Prompt/cues (7.1)		✔
Repetition and substitutions	Behavior substitution (8.2)	✔	✔
	Graded tasks (8.7)		✔
Comparison of outcomes	Credible source (9.1)	✔	
	Pros and Cons (9.2)	✔	
	Comparative imagining of future outcomes (9.3)	✔	
Reward and threat	Future punishment (10.11)	✔	
Regulation	Reduce negative emotions (11.2)		✔
Antecedents	Restructuring the physical environment (12.1)		✔
Identity	Identification of self as a role model (13.1)		✔
	Framing/reframing (13.2)	✔	✔

BCT—Behavior change technique.

**Table 2 nutrients-15-04653-t002:** Data collection and time points for the Healthy Gut Diet Study from baseline to 36 weeks gestation.

Outcome Measure	Baseline (11 to 18 Weeks)	14 to 27 Weeks	28 to 40 Weeks	36 Weeks
GDM diagnosis (primary outcome)	✓ (Eligibility)		✓	✓
GDM management	✓		✓	✓
Anthropometric data	✓			✓
Demographic information	✓			
Medical history	✓			
Depression screening	✓			✓
Physical activity	✓			✓
Dietary intake	✓	✓	✓	✓
Microbiota analysis	✓			✓
Maternal and infant outcomes				✓
Satisfaction with care				✓

## Data Availability

The data presented in this study are available on request from the corresponding author. The data are not publicly available due to privacy restrictions and conditions of ethical approval.
